## Abstract

**Background:**

Sepsis sequelae include critical illness polyneuropathy, myopathy, wasting, neurocognitive deficits, post-traumatic stress disorder, depression and chronic pain. Little is known howlong-term sequelae following hospital discharge are treated. The aim of our study is to determine the effect of a primary care-based, long-term program on health-related quality of life in sepsis survivors.

**Methods/Design:**

In a two-armed randomized multicenter interventional study, patients after sepsis (n = 290) will be assessed at 6, 12 and 24 months. Patients are eligible if severe sepsis or septic shock (ICD-10), at least two criteria of systemic inflammatory response syndrome (SIRS), at least one organ dysfunction and sufficient cognitive capacity are present. The intervention comprises 1) discharge management, 2) training of general practitioners and patients in evidence-based care for sepsis sequelae and 3) telephone monitoring of patients. At six months, we expect an improved primary outcome (health-related quality of life/SF-36) and improved secondary outcomes such as costs, mortality, clinical-, psycho-social- and process-of-care measures in the intervention group compared to the control group.

**Discussion:**

This study evaluates a primary care-based, long-term program for patients after severe sepsis. Study results may add evidence for improved sepsis care management. General practitioners may contribute efficiently to sepsis aftercare.

**Trial registration:**

U1111-1119-6345. DRKS00000741, CCT-NAPN-20875 (25 February 2011).

## Background

Sepsis is a worldwide major health concern with increasing incidence [1]. About 85,000 patients a year survive severe sepsis or septic shock [2,3] in Germany. Main sepsis sequelae include critical illness polyneuropathy/myopathy, cognitive deficits and chronic pain, all symptoms of neuronal degeneration [4-7]. In addition, post-traumatic stress disorder (PTSD) and depression are prevalent after stress exposure in the intensive care unit (ICU) [8,9].

Thus, the majority of sepsis survivors suffer from a considerable deficit in physical and psycho-social functions [10], showing a reduced health-related quality of life [11-13]. In addition to the individual burden, sepsis causes significant health economic costs, about four to seven billion Euro/year for Germany alone, including indirect costs due to loss-of-work [3].

At least, sepsis sequelae are considered to be generic for symptoms after critical illness in general [13], which is of even more clinical and socioeconomic relevance.

To improve care for long-term conditions, coordination of the fragmented process by structured interventions is effective [14]. The British National Institute for Health and Clinical Excellence’s guideline *Rehabilitation after critical illness* states that *‘*evidence is often missing and only incorporates aftercare for up to three months’ [15]. Based on a current systematic review, few follow-up interventions have been published [16]. Of these, Hacking *et al*. observed functional improvement of amputations associated with sepsis by an intensive rehabilitation program [17]. Jones *et al*. presented an increase of physical function in 126 critical illness patients who were provided a self-help manual for six months [18]. A British pilot study of Jackson *et al*., with 21 critical care patients, showed a non-significant reduction of post-traumatic symptoms using an in-house, multifaceted telemedicine program [19]. In contrast, a home-based rehabilitation program for eight weeks did not lead to better health-related quality of life or to better physical function in Australian critical illness patients [20]. A nurse-based translational pilot program that incorporated case management for patients with chronic critical illness was not effective for clinical or psycho-social outcomes [21,22].

After ICU care and hospital-based rehabilitation, most sepsis survivors receive aftercare from their primary care physician, as with most chronically ill patients. This setting is characterized by a long-lasting doctor-patient relationship, with all health services being coordinated [23]. Primary care-based interventions to improve sepsis sequelae are still rare [16].

This study will evaluate the effects of a primary care-based intervention to improve aftercare for sepsis survivors.

## Methods/Design

### Aim of the study

This study will evaluate whether health-related quality of life (SF-36) and further clinical, psycho-social, process-of-care outcomes and costs of sepsis survivors will be improved by a primary care-based, sepsis-specific aftercare program.

### Scientific hypothesis

After six months, the intervention group will show an improved primary outcome (SF-36) compared to patients with usual care in the control group.

### Study design

The study is a multicenter, prospective, two-armed randomized controlled trial. Since the intervention could compromise educational elements for primary care physicians and patients, we are not able to perform a blinded intervention. GPs are allocated only to one patient - either to the control or intervention group.

### Sample size

A wide range of effect sizes is found in comparable studies. Jackson *et al*. [19] reported that for executive functioning ability a Cohen’s d =1.1 Elliott *et al*. [20] reported that for the SF-36 physical and mental summary scores, Cohen’s d = 0.14/0.13, respectively. For our study, we assume a medium Cohen’s d = 0.5 for our primary outcome, which is between these ‘extreme values’.

With a statistical power of 90% and a significance level of 0.05, we need n = 172 patients at T2 for two-sided tests. Assuming a 40% drop-out rate [24] and 30% mortality [25], 290 patients are needed at T1.

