### Randomization

Given the GP’s written consent, patients are randomized in the intervention versus control group with n = 145 patients per group. Randomization sequence is computer-generated and provided in a sealed opaque envelope.

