### Data analysis

Randomization process will be proofed using binary logistic regression. The dependent variable logarithmic odds ratio of patient is in the intervention versus control group. As predictors, we use potential confounders (for example, socio-demographic or clinical variables). Primary outcome will be analyzed based on a two-sided t-test. Secondary endpoints will be analyzed depending on scale level, using descriptive or hypothesis generating test procedures. For evaluation of average treatment effects, we will analyze the outcome variables with a generalized analysis of covariance (g-ANCOVA) and control for potential confounders. Based on these results, we are able to adjust means, which are comparable with outcome means of a perfect randomized and balanced design [49,50].

Furthermore, mortality is taken into account. Using survival analysis models, we are able to examine the relationship between mortality and treatment. In this way, we also try to identify mortality risk factors.

Finally, we plan cost-effectiveness analyses. Therefore, we sum up the costs of micro interventions and compare the averages of treatment and control group using g-ANCOVA (see above).

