### Description of risks

Showing 6- month mortality of more than 30% [25], severe sepsis ranks among critical long-term conditions. Serious risks or undesired effects of completing questionnaires have not been reported by clinical expertise of the scientific experts in the advisory board of the study (see Additional file 1). There are no specific risks related to the intervention. Thus, there are no rules for stopping the intervention.

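### The 290 patients cover a total loss of about 40%, but the sample-size section lists 40% drop-out and 30% mortality; if these are separate losses, power is about 78%, not 90%

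*Protocol article*

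**What the plan says.** The Sample size section of the protocol article fixes the effect size ("we assume a medium Cohen’s d = 0.5 for our primary outcome") and derives the evaluable number from it: "With a statistical power of 90% and a significance level of 0.05, we need n = 172 patients at T2 for two-sided tests". It then goes from T2 back to T1: "Assuming a 40% drop-out rate [24] and 30% mortality [25], 290 patients are needed at T1". Each rate has its own citation, and nothing says that one includes the other.

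Three other sections bear on this:

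- Scientific hypothesis sets the primary comparison at six months, which is T2.
- Description of risks gives the mortality figure a time frame, with the same citation as in the sample-size sentence: "Showing 6- month mortality of more than 30% [25".
- Randomization gives the split of the 290: "patients are randomized in the intervention versus control group with n = 145 patients per group".

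The planned analysis is simple: "Primary outcome will be analyzed based on a two-sided t-test".

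**The concern.** The sentence names two reasons why a patient at T1 may have no SF-36 score at T2, but the number it arrives at has room for about one of them. Mortality is a real loss for this endpoint. The SF-36 is completed by the patient, deaths within six months fall before the primary assessment, and the planned t-test gets its power from the number of patients with a score.

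At stake is the type II error. The plan accepts 10%. If drop-out applies to patients who survive, so that the two losses compound, the type II error is about 22%. There is little slack in the effect size: the same section cites a comparable trial with d = 0.14 and 0.13 for the SF-36 summary scores.

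**Working it through.** **Inputs, all from the protocol article.** d = 0.5, two-sided alpha 0.05, power 90%, 172 evaluable at T2, drop-out 40%, mortality 30%, 290 at T1 (Sample size); 145 per group (Randomization); two-sided t-test (Data analysis).

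**1. The evaluable number.** Power of the two-sample t-test with n per arm comes from the noncentral t distribution with 2n − 2 degrees of freedom and noncentrality d·√(n/2). For d = 0.5:

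- n = 85: power 89.99%
- n = 86: power 90.3%

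So 86 per arm, or 172 in total. The plan's figure reproduces exactly.

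**2. The loss that 290 implies.** 172/290 = 0.593 retained, a total loss of 40.7%. Inflating for 40% alone gives 172/0.6 = 286.7, or 287, close to 290.

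**3. Number needed at T1 under each reading of the two rates.**

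- 40% is the total, deaths included: 172/0.60 = 287
- Separate, in sequence: 172/(0.6 × 0.7) = 172/0.42 = 409.5, or 410
- Separate, fully additive: 172/(1 − 0.4 − 0.3) = 172/0.30 = 573.3, or 574

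**4. What 290 delivers under each reading (power for d = 0.5, and the d that has 90% power).**

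| Reading | Evaluable at T2 | Power, d = 0.5 | d with 90% power |
|---|---|---|---|
| 40% is the total, deaths included | 290 × 0.60 = 174 | 91% | 0.49 |
| Separate, in sequence | 290 × 0.42 = 121.8, about 122 | 78% | 0.59 |
| Separate, fully additive (outer bound) | 290 × 0.30 = 87 | 64% | 0.70 |

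**5. What the favourable reading implies.** If 30% die and the total loss is 40%, all other loss is 10 percentage points of those enrolled. Among survivors that is 10/70 = 14.3%. Description of risks puts six-month mortality above 30%, so about 14% is the most that this reading allows.

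**6. Another possible route to 290.** Multiplying instead of dividing gives 172 × (1 + 0.4 + 0.3) = 292.4, also near 290. That is not a valid inflation for loss, and the resulting number still does not cover both losses.

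**The case against.** The strongest defence is that the 40% was meant as total attrition, with the 30% mortality named as its main part. The number fits this reading: 290 retains 59.3%, 174 patients would be evaluable, and power would be 91%. Then only the wording is at fault. The text does not exclude this reading, so the objection stands to that extent, and the power loss has to be stated as conditional. It does not remove the point. The sentence gives the rates side by side with separate citations, and the favourable reading carries an assumption of at most about 14% other loss among survivors that appears nowhere. Nor is this a detail left to a fuller document, since the article prints both the rates and the result.

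A reader might infer more than the document supports in four ways:

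- *That mortality was simply forgotten.* The mistaken multiplication above also lands near 290, so how the figure was reached cannot be settled from the text. What can be said is which total loss 290 covers.
- *That power is 64%.* This needs drop-out and death to be disjoint shares of all enrolled patients, a 70% loss by six months. Nothing in the protocol states that. It is an outer bound only.
- *That refusals by general practitioners deplete the 290 further.* Sample size counts the 290 at T1, but Randomization allocates 145 per group, 290 in total, after the practitioner's written consent. Refusals therefore fall outside the 290.
- *That the planned covariate-adjusted analysis makes up the loss.* The size of any gain depends on a correlation between baseline and outcome that the protocol does not give.

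**Conclusion.** The 290 does not follow from the two loss rates as written. It covers a total loss of about 40%. Read as two losses acting in sequence, the stated inputs call for about 410 patients; 290 leaves about 122 evaluable, power is about 78% for d = 0.5, and 90% power holds only for d = 0.59.

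It would go too far to conclude that the trial is underpowered. If the 40% includes the deaths, 290 is sufficient and the 90% stands. The firm part is that the protocol does not say which reading applies, and the stated power depends on it. The figures assume equal arms, equal loss in both arms, the t-test named in the protocol, and both rates applying between T1 and T2.

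**What to change.** Correct the sentence without changing the sample size, in one of two ways:

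- State that 40% is the total expected loss at T2 including deaths, and that other loss is therefore assumed to be at most about 14% of survivors. The evaluable number is then 174, and the 90% power stands.
- Keep drop-out and mortality as separate losses, and restate the evaluable number at T2 as about 122 and the power as about 78% for d = 0.5, with 90% power for d = 0.59.

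The choice should follow from what the 40% in the cited source counts, which the sponsor can check. Either way the cost is a change of wording and no extra patients. The second option also means a less favourable stated power.

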### Data collection

Patients will be recruited from 20 ICUs in nine study centers across Germany (see Additional file 1). Eligible survivors of severe sepsis or septic shock are screened on a daily basis by ICU consultants and reported to the study team. Within one month after discharge from ICU, patients are contacted by a study physician and asked to participate in the study. For eligibility, a cognition test is performed [26]. All patients are informed about the study course.

Within one month after discharge from ICU, the first data set (T1) is collected by the study nurse, including clinical and socio-demographic characteristics. At the same time, the liaison physician contacts the responsible general practitioner (GP) by telephone to ask for study participation.

### Randomization

Given the GP’s written consent, patients are randomized in the intervention versus control group with n = 145 patients per group. Randomization sequence is computer-generated and provided in a sealed opaque envelope.

### Inclusion criteria

Patients are eligible on the presence of severe sepsis or septic shock, as defined by the definitions of the German Sepsis Society [27]. Two systemic inflammatory response syndrome (SIRS) criteria have to be completed and at least one organ dysfunction (see Additional file 2). Inclusion criteria are checked by the participating ICU doctors.

Furthermore, patients must be 18 years or older and capable of sufficient German language skills.

### Exclusion criteria

Patients are excluded from study participation due to insufficient German language skills, deafness, blindness or speech impairment. Furthermore, patients suffering from severe cognitive impairment are not eligible for study participation (determined by a telephone interview of cognitive status (TICS-M) ≤27 points) [26].

### Intervention treatment

The intervention contains three main components:

1. Discharge management with structured information between inpatient and outpatient care in accordance with the transitional care model [28], which was shown to reduce costs and rehospitalization rates [29].

2. Training of GPs and patients in sepsis sequelae and evidence-based treatment options [30]. A special focus lies on an effective self-management of patients, which improves health-related quality of life in post-intensive care patients [31].

3. Monthly telephone monitoring of patients through specifically designed telephone interviews is provided for 12 months regarding sepsis sequelae symptoms. Systematic monitoring improves the physician-patient interaction and supplies relevant information on patient clinical status to the GP, according to the chronic care model [32,33].The intervention is delivered by a study center-based case manager and a liaison physician (see Figure 1). The case manager is a nurse by qualification, trained in sepsis aftercare. She acts as an attendant for the patient, asking about the patient’s health constitution and actual problems, and provides training and monitoring. The liaison physician as the GP’s contact person is responsible for the education and reporting of the monitoring results and offers feedback if required. The liaison physician also determines further patient educational elements to the case manager.

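### Case managers and liaison physicians act in the intervention arm only, but the primary t-test and the sample size treat all 172 patients as independent

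*Protocol article*

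**What the plan says.** All places are in the protocol article.

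- **Delivery (Intervention treatment).** "The intervention is delivered by a study center-based case manager and a liaison physician". The case manager, a trained nurse, educates and monitors the patient. The liaison physician trains the GP and passes on the monitoring results. The number of people in either role is not stated.
- **Control (Control treatment).** Usual care by GPs and specialists, with no counterpart to either role.
- **Setting (Data collection, first section of that name).** "Patients will be recruited from 20 ICUs in nine study centers across Germany".
- **GPs (Study design; Limitations).** Each GP has one trial patient only. This is presented as protection against contamination.
- **Primary test (Data analysis).** "Primary outcome will be analyzed based on a two-sided t-test". A generalized analysis of covariance controlling for potential confounders is also planned. The examples named are socio-demographic and clinical variables.
- **Sample size (Sample size).** "With a statistical power of 90% and a significance level of 0.05, we need n = 172 patients at T2 for two-sided tests", with "d = 0.5 for our primary outcome". No allowance for clustering appears.

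**The concern.** This is a partially nested design. Intervention patients are grouped under whoever trained and monitored them, while control patients are not grouped at all. One patient per GP removes clustering at practice level, but nothing comparable is said of the case manager or liaison physician, who can each serve many patients.

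If some operators achieve more than others, their patients' SF-36 scores move together, and the intervention mean is less certain than 86 independent patients would make it. The t-test cannot see this. Its interval is then too narrow for a statement about the program as such, and a good operator cannot be told from a good program. That matters because the Strengths/conclusion section presents the program as a possible addition to sepsis aftercare, where other people would deliver it.

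**Working it through.** **1. The plan's own figure.** For d = 0.5, two-sided alpha 0.05 and 90% power, the noncentral-t solution is 85.03 per arm. This rounds up to 86 per arm, or 172 in total (power 90.3%). With the 40% loss, 172/0.60 = 287, close to the stated 290. The 172 therefore reproduces with every patient independent and no design effect.

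**2. Inputs for the check.** From the article: 86 per arm at T2, d = 0.5, alpha 0.05. Assumed, because the article gives neither: k operators in the intervention arm (3, 9 or 18; nine would be one per study centre) and an operator ICC of 0.01, 0.02 or 0.05.

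**3. Formulas.**
- Patients per operator: m = 86/k.
- Variance inflation of the arm difference, with clustering in one arm only: V = 1 + (m − 1) × ICC/2.
- True standard error divided by t-test standard error: √V.
- Real two-sided error: 2 × (1 − Φ(1.96/√V)).
- Power of a test that allows for clustering: noncentral t with noncentrality 0.5/√(v_I + v_C), where v_I = (1 + (m − 1) × ICC)/86 and v_C = 1/86. Satterthwaite degrees of freedom: (v_I + v_C)² / [v_I²/(k − 1) + v_C²/85].

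**4. One case in full: k = 9, ICC = 0.05.** m = 86/9 = 9.56. V = 1 + 8.56 × 0.05/2 = 1.214, so √V = 1.102. Error = 2 × (1 − Φ(1.96/1.102)) = 2 × (1 − Φ(1.779)) = 7.5%. For power, v_I = 1.428/86 = 0.01660 and v_C = 0.01163. The noncentrality is 0.5/√0.02823 = 2.98 on 22.1 degrees of freedom, which gives 81.2%.

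**5. Results.** The simulated error is that of the plain t-test, with 20,000 runs per case.

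| Operators | ICC | m | √V | Error, formula | Error, simulated | Power, small-sample df |
|---|---|---|---|---|---|---|
| 3 | 0.01 | 28.7 | 1.067 | 6.6% | 6.5% | 73.4% |
| 3 | 0.02 | 28.7 | 1.130 | 8.3% | 8.3% | 65.8% |
| 3 | 0.05 | 28.7 | 1.301 | 13.2% | 13.4% | 48.4% |
| 9 | 0.01 | 9.6 | 1.021 | 5.5% | 5.6% | 87.2% |
| 9 | 0.02 | 9.6 | 1.042 | 6.0% | 5.7% | 85.7% |
| 9 | 0.05 | 9.6 | 1.102 | 7.5% | 7.4% | 81.2% |
| 18 | 0.01 | 4.8 | 1.009 | 5.2% | 5.1% | 89.1% |
| 18 | 0.02 | 4.8 | 1.019 | 5.4% | 5.5% | 88.5% |
| 18 | 0.05 | 4.8 | 1.046 | 6.1% | 6.3% | 86.7% |

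At ICC = 0 the simulated error was 4.9% to 5.2% for these three values of k. Part of the power loss comes from the fewer degrees of freedom. With nine operators, variance inflation alone gives 89.4%, 88.2% and 84.5%.

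**6. Centre, checked separately.** With centre effects shared by both arms (centre ICC 0.02 to 0.10, nine centres, no operator effect), the plain t-test had an error of 4.2% to 4.7% when arms were balanced within centre, and 4.6% to 5.2% when allocation ignored centre. Adding a balanced shared centre effect of 0.05 to nine operators with ICC 0.01, 0.02 and 0.05 gave 5.0%, 5.4% and 6.6%. Leaving centre out does not narrow the interval; operator effects confined to one arm do.

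**The case against.** **Both inputs are assumed.** The article gives no count of operators and no ICC. With about nine operators and an ICC of 0.01 to 0.02, the standard error is too small by only 2% to 4%. Case managers are trained, manuals cover training content and monitoring instruments, and a traffic-light scheme grades urgency. All of this plausibly limits differences between operators. This stands, and it is why the size is given as a range. A reader might infer that only a handful of people deliver the program; the text does not say so, and the 13% figure needs both three operators and the highest ICC in the table.

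**The target of inference matters.** If the conclusion is confined to the operators who took part, the t-test standard error is not too narrow. If no operator has any effect, the error is 5%. This also stands. But the article argues for the program in general, and that wider claim needs operator variation to be counted.

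**Adjustment is already planned.** The covariance analysis has an open list of confounders, which may include centre. Further models may be in an analysis plan not shown. This stands only in part: the t-test is stated as the primary test, and a covariate list does not model correlation that exists in one arm only.

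**Allocation.** From "Randomization sequence is computer-generated and provided in a sealed opaque envelope" a reader might infer that allocation was not stratified by centre and that small centres could become lopsided. The description is a short summary in a condensed article. Its silence does not show the absence of strata, so no claim about imbalance is made here.

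**Conclusion.** The point holds in a conditional form. The stated test and sample size take no account of operators who act in one arm only. If operators differ, the standard error is too small for a conclusion that reaches beyond them.

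On the assumed range, the effect is modest with nine operators (error about 5.5% to 7.5%, power about 87% to 81%) and smaller with eighteen. It becomes serious only with very few (error about 6.5% to 13% with three). It vanishes if operators do not differ. The article does not let a reader tell which case applies.

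A stronger reading, that omitting centre from the test makes the error bars too narrow, is not supported: shared centre effects left the error at or slightly below 5%. The point is worth acting on because the remedy is cheap and, according to the Trial status section, recruitment was still under way. It does not invalidate the design.

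**What to change.** 1. State how many case managers and liaison physicians deliver the program, and record both for each intervention patient.
2. Include study centre as a factor in the primary SF-36 model. This is for precision and chance imbalance between centres; it does not cure operator clustering.
3. Pre-specify a sensitivity analysis with an operator random effect in the intervention arm only (a partially nested model) and small-sample degrees of freedom.
4. State in advance how the conclusion will be qualified if that analysis differs from the primary result, for example by confining it to the operators who took part.

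**Cost.** Two recorded fields per intervention patient, one further model, a few degrees of freedom for centre, and a wider interval in the sensitivity analysis if operators differ. With very few operators that interval will be wide and the operator variance poorly estimated, which the report should say. No increase in sample size and no change to the allocation list is asked for.
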